## Methods

### Trial design

This research is conducted as a parallel randomized clinical trial with follow-up. The study subjects are randomly allocated into intervention and control groups.

### Participants

The study population is children and adolescents diagnosed with ALL or other cancer outside the central nervous system (e.g. Hodgkin and non-Hodgkin Lymphomas, neuroblastoma, Wilms tumor, rhabdomyosarcoma, retinoblastoma and Ewing sarcoma). The treatment for different forms of cancer varies considerably, however; one inclusion criteria is that the treatment regimen has to include vincristine. The treatment duration and dose is taken into account in the data analyses. Patients with central nervous system tumors are not included as these tumors may cause severe and more permanent motor performance difficulties complicating the study design. In addition, these conditions may require brain surgery and the physical activity and exercise recommendations may have great individual differences, even though these patients would also benefit from physical activity.

The eligibility criteria to this study are: 1) the patients are aged 3–16 years at the time of recruitment, 2) the treatment regimen includes vincristine and 3) the patient is treated in either of the designated hospitals (Turku University Hospital or Tampere University Hospital, Finland). The lower age limit of 3 years for the first inclusion criterion is chosen because in the included group 3-year-old children are estimated to be the youngest that may have the competence to learn to play the easiest active video games of Wii™ Fit (Nintendo Co., Ltd., Kyoto, Japan). Also the motor performance measure Movement ABC-2 (MABC-2, 2nd Edition, Pearson Education, Ltd., London, UK) is designed to measure 3- to 16-year-old children’s motor performance [43]. The second inclusion criterion is chosen because the sample is aimed to be as comparable and homogeneous as reasonably possible and because the homogeneity in this sample varies in many other ways such as age and diagnosis. In addition, vincristine treatment may cause peripheral neuropathy increasing the need of physical activity and exercise. The sampling method used in these two university hospitals is simple random sampling—all new patients meeting the eligibility criteria are given the possibility to be included. Together, these two hospitals treat approximately 40% of the pediatric cancer patients in Finland, which accounts for 20–30 new cases eligible for this study annually. The participants are excluded if they have other diseases limiting their physical or cognitive function, epilepsy, or they are not able to communicate in Finnish, Swedish or English. The target sample size is calculated from the main outcome, using a power analysis.

### Recruitment

Children are asked to participate within a week of their primary cancer diagnosis, or as soon as possible after that. The attending physician verifies the children’s eligibility for the study and contacts the researcher. Eligible children and their caregivers receive written and oral age-appropriate research information from the researcher, and informed consent is obtained the next day at the earliest. The family may consider, for as long as necessary, whether to participate. The children need to give their consent at least verbally and parents sign the written informed consents. In addition, children who have already learned to write their name sign their own written consents. According to Finnish legislation, participants over 15 years old may individually decide whether they are willing to participate [44]. The recruitment will continue until the target sample size is achieved.

### Intervention

The physical activity in the intervention is based on active video gaming. The intervention consists of playing elective active Nintendo Wii™ games daily, for at least 30 minutes, during hospitalization and at home for 8 weeks in total, with consideration of the participants’ individual conditions. Physical activity is not allowed during fever and vomiting or nausea episodes, or if the medical condition changes acutely. The physical activity intensity is recommended as light-to-moderate. One way to monitor the relative intensity of activity is to monitor the respiration and breathing rate during the activity [45]. The parents are guided that light-to-moderate intensity physical activity equals only to slightly increased breathing rate, still feeling “easy to breath” or “slight breathlessness” and they are advised to monitor the child’s condition before and during the physical activities. At the beginning of the study, the attending physician verifies the children’s ability to physical activity, and, if there are significant changes to the child’s condition, the researcher and the physical therapists who conduct the motor performance testing are informed. The children receiving anthracycline therapy are also followed by a cardiologist and regular echocardiograms.

The intervention includes information and recommendations for physical activity and guidance on which Nintendo Wii™ Fit games to play and how to play them. All children in the intervention group will receive the same written instructions and individual face-to-face teaching, where examples about suitable games for each age group are presented. For 3- to 6-year-old children, games such as Hola hoop or Jogging are recommended based on the easiest difficulty levels. For children aged 7- to 10-years, the recommended games include such as Island Cycling, Rhythm Kung-Fu, Hola hoop and Jogging and for 11- to 16-year-old children there are recommended games from all the four types of exercises (aerobics, balance, strength training, yoga). This guidance and instruction are given by a physiotherapist in the hospital. The physiotherapist contacts the participants in the intervention group via telephone for consultation during the intervention in order to encourage children to play and be active. Children in the intervention group have the game console and games at home for the duration of the intervention period.

Some limitations of the intervention must be mentioned: children may learn to play the games with incorrect execution of movements, which decreases the amount of activity while playing. However, the physical therapist teaches the games to the intervention group as they should be played, and parents are guided to watch that the children play them correctly. It is also more difficult to cheat the balance board used in the intervention than the remote control, and even if the child is executing a movement incorrectly, playing the game still needs advanced coordination with the timing of the movements. The second concern about the intervention is that how well the smallest enrolled children can experience success when playing the game. Too difficult tasks may promote boredom and unsatisfactory commitment to the program. This might be the case among the very youngest children enrolled to the study. However, our experiences have been positive so far. After this study we get valuable directions to develop the intervention further and even new easier activity promoting video games might have come to the market.

If the children or guardians have questions about the intervention or physical activity recommendations they are guided to contact the ward or the research group. If the question is about the child’s health, they are guided to contact the ward staff. Both study wards and their staff are well informed about the ongoing study and will let the researcher know of any questions concerning the study or its procedures.

In this study, the control group receives only general advice for physical activity for 30 minutes per day. They do not receive guidance on playing active video games or telephone consultations after being discharged from the first medical treatment period. The controls have the normal treatment so that if they need physical therapy referral or consultation from a physical therapist they will receive the normal treatment similarly as the children in the intervention group. All the physical therapy session documentation is collected in the end of the study and will be taken into consideration when analyzing and reporting the data.

### Outcome measurements and time-points of assessments

The main outcomes*—physical activity* and *sedentary behavior*—*,* are measured with four different outcome measures. The main outcome measurement device for physical activity is a three-dimensional accelerometer, The Fitbit Tracker (Fitbit, Inc., San Francisco, CA). An accelerometer is a motion sensor which detects changes in movement. An accelerometer provides a valid and reliable assessment about achieving objective data of children’s physical activity [46]. We have not found a published validation study about the Fitbit Tracker (Fitbit, Inc., San Francisco, CA) so far but our research group will conduct a validation study before the data analysis of this study to fulfill this limitation. The accelerometer is used at 1^st^ week of the intervention and at 1 year. The device is worn for one week at a time so that the measurement includes both week and weekend days. It is worn on the waist. Attaching accelerometer to waist it is relatively close to the body’s center of gravity and vertical movements are comparable to energy expenditure [47]. The accelerometer is not waterproof, so the study participants are guided to remove it while taking a shower or swimming. The times accelerometer is not worn are reported and given to the researcher when returning the accelerometer. Physical activity is also measured with two questionnaires and a self-assessment activity diary.

The first physical activity questionnaire assesses leisure-time physical activity in metabolic equivalent (MET) hours (METh) per week. The questionnaire contains multiple-choice questions about physical activity intensity, duration and frequency and it is widely used self-reported questionnaire [48]. The questionnaire has previously been used in studies of children’s and adolescents’ physical activity and vascular health [49-51]. The questionnaire correlated relatively well with the accelerometer data (r = 0.26–0.40) and pedometers (r = 0.30–0.39) [50]. For the children under 10 years old, this questionnaire was modified, the parents filling it in as a proxy report of their child. The other activity questionnaire was developed for this study and adds questions about the children’s physical activity and sedentary behavior, such as how much time the children spend in sedentary screen-based activities. The questions are divided into categories: sedentary behavior, light activities, moderate activities and vigorous intensity activities [52]. Report estimates the amount of these activities during a normal day.

The activity diary is completed for one week at every measurement point. The measurement points are: at baseline, 2 months, 6 months, 1 year and 2.5 years after the baseline. Using the activity diary data, we get self- and proxy-reported estimates about the frequency and duration of activity. Behaviors and activities are collected in 10-minute periods 24 hours a day, and the activities that are filled in the diary are divided into categories (sleeping, being awake but lying in bed, being awake and sitting, light activity, moderate activity, vigorous activity or playing active video games). Hence, the child’s acts are collected during the whole 24 hours for seven days in every measurement points. Moreover, the intervention group fills out a special game diary to separate the active videogame playtime and different games they play from other activity. The self- or proxy reported data from the diaries may not be precise but it will give directions and add valuable information to the objectively collected data.

According to literature, children under 10 years old may not be cognitively able to recall and report their physical activity reliably [53]. Therefore, 3- to 9-year-old children’s guardians fill out the questionnaires as a proxy report. Children aged 10 to16 years fill out the questionnaires independently. The questions have some age related modifications depending on whether the child or the guardian is designed to fill the questionnaire.

*Motor performance* is measured with the Movement Assessment Battery for Children (M-ABC) test [54,43]. The revised version M-ABC2 has organized the test age bands from 3 to 6, from 7 to 10 and from 11 to 16 years, so the test is suitable for the studied age group and it has age-related scores (3–16) [43]. The M-ABC2 has been established as a valid instrument for measuring children’s motor skills [55] and has been successfully used among cancer patients [56]. The M-ABC2 measures standardized tasks in three categories: manual dexterity skills, ball skills and balance skills [43]. The motor performance assessments are conducted during the inpatient stays or as a part of their normal treatment or control visits. If possible, the patients are not connected to any medical devices during the testing, and the testing is conducted in a therapy or test room that physical therapists use near the treatment ward. In some circumstances, if needed, the test may be conducted in the patient’s room. Depending on the child’s condition, some parts, i.e. jumping or balancing, might have to be skipped. All the modifications or skipped tasks and the reasons for those are documented carefully and considered during the data analyzes.

Children’s self-reported *fatigue* is reported by standardized PedsQL Multidimensional Fatigue Scale questionnaires. The PedsQL questionnaires have age-related scores, including the proxy report versions for parents [57]. The parents of the 3- to 4-year-old children fill in only the proxy report versions of the questionnaire. The 5- to 7-year-old children are helped to fill in the questionnaire, and their parents fill the proxy version. The 8- to 18-year-old children and their parents fill in the questionnaire independently. The PedsQL™ Multidimensional Fatigue Scale has shown fairly good internal consistency and responsiveness in measuring fatigue in children and adolescents with cancer [58].

To assess *the metabolic risk factors*, each participant’s height, weight, body mass index, resting blood pressure, waist circumference, and fasting blood sugar and insulin concentrations are measured at all measurement points. Invasive tests are carried out within the normal blood tests of the cancer treatment procedures so that no additional needle punctures into the patients are required. Metabolic risk factors are examined, since childhood cancer survivors have been shown to be more insulin resistant and have higher cardiovascular risks than healthy children [59,60].

Eight weeks after the first measurement point, each child, and guardian if the child is under 10 years old, are interviewed by the researcher (LK). This interview includes open questions about physical activity, and each child is asked about their perceptions of the most enjoyed activation methods during their cancer treatment in the hospital and at home. The aim is to find out about children’s own ideas on how they would become more active and what they would like to have in the hospital to inspire them to physical activity. The children in the intervention group are also asked about their experiences of active video gaming to gain a deeper understanding about the intervention. The interviews are voice recorded if the child and his/her family are comfortable with it and provide their consent. There are multiple aims for this qualitative section of the trial [61]. First, we want to identify the needs of this target population regarding how they would like to be motivated and activated and how that activation could manifest during periods of treatment and isolation. Second, it is useful to know the reasons for why some participants dropped out or did not participate. Third, we want the participants to describe the problems, if any, in the intervention for further research and clinical purposes. In addition, the interviews will help to evaluate and clarify the overall study findings [61].

The baseline demographics of all the participants include the time of diagnoses, type of cancer, treatment received and information of the disease status. This information is collected from the electronic health records. The time points of assessment and the outcome variables are described in Figure 1.

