### Study aims

The primary aim of this study is to evaluate the efficacy of active video games with regard to the promotion of physical activity in children with cancer. The ultimate goal is to motivate children with cancer and their families to integrate active lifestyle choices into their everyday life, even during treatment, to decrease the negative impact of high levels of sedentary behavior. The results will help answer the question of whether playing active video games has a positive effect on the health of children with cancer.

Our hypothesis is that the possibility to play active video games and guidance given to the family about physical activity during cancer treatment promote children’s physical activity and shorten sedentary periods when compared to the control group, who receive only a general recommendation to be active.

The detailed research questions and hypotheses of the study are:

1. Is playing active video games effective in increasing the physical activity of children with cancer during cancer treatment?

a) It is hypothesized that the possibility of playing active video games during cancer treatment promotes children’s physical activity compared to controls.

2. Is playing active video games effective in promoting motor performance during cancer treatment?

b) It is hypothesized that children’s motor performance in the intervention group is maintained better than in the control group.

3. Is playing active video games effective in reducing experienced fatigue by children with cancer?

c) It is hypothesized that the children in the intervention group experience less fatigue during cancer treatment than the children in the control group.

4. Do playing active video games have impact on children’s body mass index and the development of metabolic risk factors in children with cancer?

d) It is hypothesized that playing active video games has a positive impact on children’s body mass index and metabolic risk factors during cancer treatment.

5. What are the children’s and families’ perceptions of the most enjoyed activation methods during cancer treatment?

The protocol follows the methodological guidelines for clinical trials outlined in the CONSORT statement [42].

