### Data analysis

The quantitative data from the activity and fatigue questionnaires, M-ABC scores, accelerometers and metabolic risk factors are to be analyzed and tested using statistical methods. Normally-distributed data will be tested for differences between the intervention and control groups by using a two-sample *t*-test and non-normally-distributed data Wilcoxon rank-sum test. Categorical variables will be tested with a chi-squared test. Multivariable analysis will be conducted with potential confounders if the researcher and statistician find it relevant. Statistical software SPSS (IBM SPSS Statistics 21) will be used. The statistical significance will be set at p <0.05.

The activity diaries will be analyzed by counting the continuous length of sedentary periods and the amount of sedentary periods lasting longer than two hours. The activity periods and their lengths will be counted and summarized. These results will be assimilated into the data from the accelerometers and compared between the groups. Activity data will also be surveyed longitudinally over the whole 2.5-year treatment time and reported as descriptive summaries. Game diaries will be analyzed by counting the duration and frequency for the gaming and the games the participants have played the most. The qualitative data from the interviews will be analyzed with content analysis.

The results will be reported following the methodological guidelines for clinical trials outlined in the CONSORT statement [42].

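### BMI, waist circumference and blood pressure are named without an age- and sex-standardised scale and go to an unadjusted two-group test across ages 3 to 16 (minor; secondary outcomes)

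*Protocol article*

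**What the plan says.** Under Study aims, the fourth hypothesis is that active video gaming "has a positive impact on children’s body mass index and metabolic risk factors during cancer treatment". Under Outcome measurements and time-points of assessments, the variables are listed: each participant's "height, weight, body mass index, resting blood pressure, waist circumference, and fasting blood sugar and insulin concentrations are measured at all measurement points". The diary paragraph of that section gives the measurement points as "at baseline, 2 months, 6 months, 1 year and 2.5 years after the baseline".

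Data analysis brings these variables under the general rule: "M-ABC scores, accelerometers and metabolic risk factors are to be analyzed and tested using statistical methods". The test is then fixed: "Normally-distributed data will be tested for differences between the intervention and control groups by using a two-sample" t-test, with the Wilcoxon rank-sum test for non-normal data. Adjustment is optional and no covariate is named: "Multivariable analysis will be conducted with potential confounders if the researcher and statistician find it relevant".

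On the age span, Participants says that "the patients are aged 3–16 years at the time of recruitment". Randomization and blinding describes random blocks of 2 to 4 and mentions no stratification by age. For M-ABC2 and the PedsQL fatigue scale, the outcome section points out that age-related scores exist. It says nothing of the kind for BMI, waist or blood pressure, and it does not say whether follow-up values or changes from baseline are compared.

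**The concern.** In children, the usual level and spread of BMI, waist circumference and blood pressure depend on age and sex. With a 13-year age span, much of the between-child variance in these measures can be age and not adiposity or risk. Three costs follow if the values enter the test as listed.

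- **Precision.** Age variance stays in the error term of a small trial.
- **Chance imbalance.** With 16 to 20 children per arm and no age stratification stated, the arms can differ in mean age. An unadjusted test then attributes that difference to the intervention.
- **Meaning.** The same raw difference is a large departure in a young child and a small one in an adolescent, so the pooled mean difference cannot be read as one effect on adiposity. Randomisation does not cure this.

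At stake is whether the metabolic hypothesis can be answered clearly, and whether scale and covariates are chosen only after the data are seen.

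**Working it through.** **1. The plan's own figure.** The sample size rests on physical activity: difference 360, SD of change 360, so the standardised effect is 360/360 = 1.0. With the noncentral t, two-sided 5%, power is 0.781 at 16 per arm and 0.807 at 17, so 17 per arm (34 in total) reproduces. No figure is given for the metabolic outcomes. The relevant sizes are 20 per arm (40 enrolled), 17 per arm (34) and 16 per arm (40 × 0.8 = 32, a 20% loss).

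**2. Is the raw comparison biased?** Simulation of an unadjusted t-test, 40,000 runs, 17 or 20 per arm, with age assumed to explain R² = 0.3 or 0.6 of the outcome variance and no true effect: rejection rate 0.049 to 0.051, mean between-arm difference about 0. So it is not biased on average.

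**3. Chance age imbalance.** Assume ages uniform on 3 to 16: SD = 13/√12 = 3.75 years. The SE of the difference in mean age is 3.75 × √(2/n).

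| Per arm | SE (years) | P(imbalance > 1 y) | P(imbalance > 2 y) |
|---|---|---|---|
| 17 | 1.29 | 44% | 12% |
| 20 | 1.19 | 40% | 9% |

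In the simulated trials with an imbalance above 2 years, the unadjusted test rejects a true null about 16 to 17% of the time at R² = 0.3 and 25 to 31% at R² = 0.6.

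**4. Precision.** At 17 per arm the minimum detectable difference (80% power) is 0.99 raw SD. Removing an age and sex share R² multiplies it by √(1 − R²). The last column is the power of the raw test for an effect that the standardised test detects with 80% power.

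| Assumed R² | Detectable difference (raw SD) | Power of raw test |
|---|---|---|
| 0.1 | 0.94 | 0.76 |
| 0.3 | 0.83 | 0.65 |
| 0.5 | 0.70 | 0.51 |
| 0.7 | 0.54 | 0.34 |

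**5. BMI example.** Assumed norms, not in the documents: median 15.9 at 3 y, 15.4 at 5.5 y, 16.8 at 10 y and 20.7 at 16 y; SD rising from 1.2 to 3.1; linear in between.

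- A child of 3 with unchanged relative weight changes over 30 months by 15.4 − 15.9 = −0.5 kg/m².
- A child of 13 changes by 2.5 × (20.7 − 16.8)/6 = +1.6 kg/m².
- One kg/m² is 1/1.35 = 0.74 SD at age 4 and 1/2.95 = 0.34 SD at age 15.

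Simulation with these norms, 16 per arm, true effect 0.5 age-specific SD, correlation of z-scores between visits 0.7 or 0.85:

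| Quantity tested | Power, raw BMI | Power, z-score |
|---|---|---|
| Follow-up value | 18–19% | 27–29% |
| Change from baseline | 43–67% | 43–70% |

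The range for change reflects the two correlations. With no true effect, overall rejection is 5% on either scale. Where mean age differs by more than 2 years, the follow-up test rejects about 17 to 20% of the time in raw BMI and about 4 to 7% in z-scores.

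**The case against.** The strongest reply is that nothing in the article says raw units will be compared. The outcome section lists what is measured, and a z-score derived from recorded data can go into either named test. Choice of reference and derived variable is common analysis-plan content, these are secondary outcomes in a condensed article, and Figure 1, which lists the outcome variables, is not available here. This stands as a limit on severity. It does not remove the point: the article goes beyond listing variables, since it fixes the test and makes adjustment a matter of later judgement, and it mentions age-related scores for two other outcomes only.

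A second reply is that the one contrast the article spells out, in the sample size section, is a difference in change, where standardising gains little power. That is correct as far as it goes. But that statement concerns physical activity, and for the metabolic outcomes the article does not say which contrast is used. The simulated effect is also constant on the z-scale, which favours z-scores by construction.

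A reader might go further and infer that growth drives the comparison. It does not: both randomised arms grow, the expected between-arm difference from growth is zero, and type I error holds at 5%. Growth would dominate within-arm change, which is not what is tested.

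A reader might also want to exclude children with abdominal tumours from the waist comparison. Such tumours are expected equally in both arms, so they add noise and not bias, and the exclusion is not needed.

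**Conclusion.** The point holds in a limited form and is minor. Taken literally, the article puts unstandardised BMI, waist and blood pressure from children aged 3 to 16 into an unadjusted test with discretionary adjustment. The comparison stays valid on average, but it is less precise, exposed to chance age imbalance, and hard to interpret.

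The loss is material if follow-up values are compared (about 19% against 28% power for BMI at 16 per arm) and small if changes are compared (about 0 to 4 points). The interpretability problem applies in both cases.

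These sizes rest on assumptions that the documents do not supply: the BMI norms, uniform ages, the R² values, the between-visit correlations and an effect of 0.5 age-specific SD. No figures were worked out for waist or blood pressure specifically.

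**What to change.** In the outcome section and in Data analysis, state that:

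- BMI, waist circumference (or waist-to-height ratio) and blood pressure are converted to age- and sex-specific z-scores, for blood pressure also height-specific, from a named reference and at the exact age at each visit;
- the between-group comparison uses these values adjusted for the baseline value;
- raw values are reported descriptively.

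This replaces discretionary adjustment for these outcomes. It needs no new visit, sample or measurement, because height, weight, waist and blood pressure are already recorded at every measurement point. The small downside is that results depend to some degree on the chosen reference.
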